## Abstract

**Background:**

Cigarette smoking is highly concentrated among individuals with lower socioeconomic status (SES) who often lack access to smoking cessation services. Thus, smoking cessation in lower SES adults remains a critical public health concern that warrants further study and attention. Smokers attempting to quit are at the highest risk for lapse within the first weeks of their quit attempt, and an initial lapse is highly likely to lead to full relapse. It is essential to identify and understand behavioral factors that may increase or decrease the likelihood of successful smoking cessation among lower SES adults during a quit attempt (pre-and post-quit). Recently, sleep dysregulation, such as insufficient sleep duration, has been considered as a potential intervention target to address smoking behaviors (e.g., number of cigarettes smoked per day) and improve smoking cessation outcomes (e.g., abstinence). Recent studies have found that lower SES is associated with higher rates of poor sleep. Thus, SES should be accounted for when assessing sleep dysregulation during smoking cessation attempts. Although previous studies have examined the relationship between sleep dysregulation and smoking behavior and/or cessation outcomes, they have several methodological limitations, including the use of retrospective survey methods, use of cross-sectional study designs, relying solely on laboratory-based data collection, not assessing integrated sleep health dimensions (usually only sleep duration or quality is assessed), omitting lower SES adults who smoke, and focusing on a single pathway rather than bidirectional associations.

**Methods:**

This study will use a real-time data capture approach among lower SES adults who are attempting to quit smoking. This approach will involve a granular examination of the bidirectional and temporal associations between daily sleep dysregulation and smoking cession processes (pre- and post-quit) using smartphone-based ecological momentary assessment (EMA) and wearable sensors. Specifically, we aim to identify bidirectional and temporal associations between daily smoking abstinence and sleep dysregulation via EMA and wrist-worn sensors during the first four weeks of a smoking cessation attempt.

**Discussion:**

Findings from this study will yield preliminary data that will be used to develop and implement a Just-in-Time-Adaptive Intervention (JITAI) that aims to improve sleep health during smoking cessation.

## Background

This study seeks to elucidate the bidirectional associations between daily sleep dysregulation and smoking cessation among lower socioeconomic status (SES) adults who smoke. Tobacco use disorder is the most common substance use disorder (SUD).[1] Cigarette smoking, the leading preventable cause of morbidity and mortality in the United States, [2,3] is concentrated among individuals with lower SES.[4] Although most adults who smoke express interest in quitting and half make a serious quit attempt each year, [5] adults with lower SES often lack access to evidence-based cessation services and have worse smoking cessation outcomes than higher SES people.[6,7] Thus, smoking cessation in lower SES adults remains a critical public health concern that warrants further study and intervention.

Gaining a better understanding of the associations between sleep dysregulation and smoking behavior and cessation outcomes may enhance smoking cessation interventions for underserved lower SES adults who smoke. Sleep dysregulation increases smoking behavior (e.g., the number of cigarettes per day) and reduces the odds of a successful attempt to quit. Lower SES is associated with poor sleep, [8–15] and for that reason, studies recommend accounting for SES when examining sleep dysregulation.[16] On the other hand, sufficient sleep duration and better sleep quality have been associated with fewer cigarettes smoked per day, [17] less nicotine dependence, [18] lower withdrawal levels, [19] and fewer smoking relapses.[20] Furthermore, there is evidence that cigarette smoking negatively impacts sleep duration and quality.[21] Indeed, adults who smoke tend to experience more sleep disturbance and have less total sleep time than those who do not smoke.[22] Despite documented associations between sleep dysregulation, smoking behavior, and cessation outcomes, previous studies have several limitations, which include: 1) use of retrospective survey methods can result in recall bias, [23–26] 2) a focus on singular dimensions of sleep (usually sleep duration or quality) which limit a full understanding of these complex relationships, [18,19,27–30] 3) use of cross-sectional methods which provides a one-time “snapshot of studied relationships,” [27,31–33] 4) dependence on laboratory-based data collection, which may not reflect smoking in natural environments, [21,34–36] 5) an omission of lower SES individuals, and 6) a focus on a single pathway between sleep and smoking behavior or cessation outcomes rather than bidirectional associations.[19,21,22,37].

To address these gaps in the literature, we propose to use smartphone-based ecological momentary assessment (EMA) surveys and wearable sensors to obtain a more granular understanding of the temporal associations between daily sleep dysregulation and smoking behaviors and cessation outcomes among lower SES adults who are attempting to quit smoking. These methods will utilize daily sleep [38] and smoking measures, and assess moment-to-moment feelings, behaviors, and experiences associated with sleep and cigarette use in free-living settings.[39].

Completion of the proposed research will improve our understanding of bidirectional and temporal associations between daily sleep health and smoking maintenance, withdrawal, abstinence, and relapse processes in lower SES adults attempting to quit smoking. Study findings will inform the development of future evidence-based interventions to enhance sleep health and increase smoking cessation success in people at greatest risk of tobacco-related morbidity and mortality.

## Methods

### Study aim

This study aims to identify bidirectional and temporal associations of daily smoking abstinence and sleep dysregulation via EMA and wrist-worn sensors during the first four weeks of a smoking cessation attempt.

### Study hypotheses

Hypothesis 1. On days when participants are abstinent, they will be more likely to have poorer sleep health (shorter duration, later bedtime, longer latency, lower efficiency) that night due to withdrawal symptoms; however, the effect will be attenuated over time.

Hypothesis 2. On days when participants have slept more poorly (shorter duration, later bedtime, longer latency, lower efficiency), they will be more likely to lapse or relapse to smoking.

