### Procedure

Participants will be provided an Actiwatch, and an iCO Breathalyzer. Participants who do not have a smartphone that meets the minimum criteria to support the Insight^TM^ app [44] will also be provided a phone. Participants will be instructed regarding using the Insight^TM^ smartphone application, Actiwatch, Breathalyzer, and EMA procedures. Participants will complete questionnaires at the baseline visit, including the pre-treatment assessment of sleep, other tobacco use, past/current medical history, provide a CO breath sample to verify smoking status, and measure of neck circumference.

Participants will use the Insight^TM^ app [44] to record subjective sleep and wake times and will wear an Actiwatch to obtain objective sleep data continuously for the entire 6-week study period. At the end of the study, participants will return the Actiwatch and study phone (if they did not use their own smartphone) via mail or curbside drop-off. All participants will download the Insight^TM^ mHealth application [44], which includes a “Call Staff” function/button that automatically calls study staff (e.g., if the participant has problems completing EMAs). The Insight^TM^ app [44] also includes a “Payment” button which, when pressed, indicates the number of EMAs that have been prompted and completed and the current level of compensation based upon the up-to-the-moment percentage of EMAs completed. All participants will wear Actiwatch, complete 3 virtual visits, and complete 5 daily EMAs (i.e., 3 random,1 morning and 1 evening diaries; see Measures section for details). Participants will receive $15 for completing each visit ($45 in total) and will be compensated based upon the percentage of Daily and Random EMAs completed (i.e., $70 for completing 50%−74% of prompted EMAs, $90 for completing 75%−89% of prompted EMAs, and $120 for completing 90% or more prompted EMAs). An additional $50 payment will be awarded to participants for wearing the Actiwatch at least 90% of the time. This payment will be provided after participants return the Actiwatch. There will be additional $10 payment for those who complete the one-month follow-up survey. The use of personal vs. study-provided phones will be examined as a covariate in all analyses. Data collection is expected to be completed by August 2028.

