### Analytic approach

Descriptive statistics will summarize the distributions of outcomes and demographic characteristics. We will also explore any differences in outcomes by demographic characteristics (e.g., sex, race). If more than 10% of the outcomes are missing, methods for missing data will be considered. To identify bidirectional and temporal associations of daily abstinence and sleep dysregulation via EMA and wrist worn sensors during the first four weeks of a smoking cessation attempt (N = 80), cross-lagged models (see Fig 2) will be tested to examine 1 simultaneously) the association of sleep dysregulation with subsequent changes in daily abstinence, and 2) the association of daily abstinence with subsequent changes sleep dysregulation using Actiwatch. We will use multilevel models with lagged effects in SAS 9.4 software (SAS Institute, Cary, North Carolina) to test the temporal associations between daily sleep dysregulation and smoking abstinence. Two-level models will be conducted with 80 participants who complete the assessments over the 4 weeks of post-quit. The total number of EMAs are estimated to be 1792 ~ 2240 (80% to 100% compliance) clustered within 80 participants. The models will use an AR [1] error covariance structure to account for correlations between consecutive sleep and abstinence observations.[50] When *the outcome variable is smoking abstinence*, either sleep duration, bedtime, sleep latency, or sleep efficiency will be the predictor variable. When *the outcome variable is a nighttime sleep measure* (e.g., duration, sleep maintenance efficiency, sleep onset, sleep offset), daily smoking abstinence will be the predictor variable (alternatively, other cessation outcomes (e.g., urge) will be also tested). Variances for sleep dysregulation and abstinence measures will be decomposed to within-person and between-person components. Within-person variables will be centered at the person mean, so that positive values indicate scores higher than the person’s cross-day average. Between-person variables will be centered at the sample mean so that positive values indicate higher scores than others in the sample. A stepwise procedure will be used for variable selection, and variables from the procedure (e.g., sex, ethnicity, age, other tobacco/e-cigarette use, mental diagnosis, NRT use, BMI) will be included as covariates in all models. In addition, sensitivity analysis will be conducted to evaluate the robustness of the results from the analyses. We attend to sex as a biological variable by: 1) recruiting both sexes, 2) stratifying randomization by sex, and 3) exploring any differences in outcomes by sex.

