A potential limitation of this study is that asking participants to complete EMAs may serve as an intervention (e.g., self-monitoring alone may improve health outcomes [51]. However, multiple EMA studies that have examined substance use disorders have found that EMA methods result in little to no reactivity.[52–54] A recent study of reactivity in smokers seeking cessation treatment found that frequent EMAs were related to lower craving, anxiety, anger, hunger, and positive affect but were unrelated to abstinence.[55] Importantly, all participants will receive equal numbers of EMAs in this observational study, and those variables will be centered at the person mean. Another limitation may be the burden of the 6-week EMAs and wearing of an Actiwatch. To mitigate this burden, we will use a watch with a long-lasting battery that does not require recharging during the 6-week study period. Additionally, sleep may be affected by the current season and data collection will span all four seasons (i.e., spring, summer, fall, and winter).[56,57] This study will include time of year as a covariate to avoid the potentially confounding effect of season. We indicated alternative strategies for secondary analysis using alternative outcomes (e.g., urge, cravings) for the study.

The proposed project will be among the first to examine associations between sleep dysregulation and smoking behavior and cessation outcomes using intensive longitudinal data via EMA and wearable sensors during a scheduled smoking cessation attempt. Improving sleep health in people attempting to quit smoking has emerged as a potential non-pharmacological candidate to improve cessation outcomes.[20] This project will provide preliminary data for a future R01 study focused on providing just-in-time adaptive sleep interventions (e.g., tailored messages) among lower SES adults who are attempting to quit smoking. For instance, Cognitive Behavior Therapy-based (CBT) just-in-time adaptive interventions (JITAI) that integrate sleep hygiene components [58] (e.g., maintaining a regular sleep routine, mindfulness training prior to the quit attempt, and/or CBT for sleep deprivation during cessation may be used to improve sleep health, which in turn may improve cessation outcomes. In addition, future studies may integrate other health behaviors that may mediate and/or moderate sleep dysregulation, smoking behavior, and cessation outcomes (e.g., physical activity or other substance use).

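### Hypothesis 1 predicts an abstinence effect that fades over time, but no stated model term tests this, and without day since quit a shared time trend can distort the abstinence–sleep coefficient

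*Protocol article*

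**What the plan says.** Under Study hypotheses, Hypothesis 1 has two parts. Abstinent days are followed by poorer sleep, and "however, the effect will be attenuated over time".

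The Analytic approach section sets out how this will be tested:

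- Model: "We will use multilevel models with lagged effects in SAS 9.4 software", fitted to 80 participants over the four post-quit weeks, with an AR(1) error structure.
- Predictor when a sleep measure is the outcome: "daily smoking abstinence will be the predictor variable".
- Centring: "Within-person variables will be centered at the person mean, so that positive values indicate scores higher than the person’s cross-day average".
- Covariates, chosen by a stepwise procedure: "e.g., sex, ethnicity, age, other tobacco/e-cigarette use, mental diagnosis, NRT use, BMI) will be included as covariates in all models".

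Two further covariates appear elsewhere. Procedure says: "The use of personal vs. study-provided phones will be examined as a covariate in all analyses". The Discussion says: "This study will include time of year as a covariate to avoid the potentially confounding effect of season".

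None of these places names study day or day since quit as a main effect, as an interaction with abstinence, or as a detrending step.

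**The concern.** Attenuation is a statement about how the abstinence coefficient changes with time since quitting. A model with a single within-person abstinence coefficient averages over the 28 days and has no parameter that answers the question. Followed as written, the plan leaves part of Hypothesis 1 untested.

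The second issue concerns the coefficient that the model does estimate. In the weeks after a quit date, both abstinence and sleep may drift. If they do, early days and late days differ on both, and the within-person comparison picks up that difference as if abstinence caused it. Centring at the person mean removes stable differences between people, not a change within people that follows the calendar of the quit attempt. AR(1) errors describe correlation between neighbouring residuals, not a moving mean. Time of year is calendar season and does not stand in for day since quit. At stake is whether a reported abstinence–sleep association, in either direction of the cross-lagged analysis, reflects the two behaviours or only the passage of time.

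**Working it through.** **Inputs.** From Analytic approach: 80 participants and 28 post-quit days. 80 × 28 = 2,240 person-days, and 0.80 × 2,240 = 1,792, which reproduces the article's range. From Power: ICC 0.2. The article gives no trajectory for abstinence or for sleep, so the trends below are assumptions. Sleep is in SD units and d is day since quit scaled from 0 to 1.

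**Step 1: what the stated model estimates.** With A for abstinence, the description amounts to

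sleep(i,t) = intercept(i) + bW × [A(i,t) − mean A(i)] + bB × [mean A(i) − grand mean] + covariates + AR(1) error.

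bW is one number. Attenuation needs bW + bWT × d, and bWT is not in the stated model.

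**Step 2: fading against constant.** Let the effect be −0.4 × (1 − d), with abstinence at 50% throughout. Its average is (−0.4 + 0)/2 = −0.20. In 300 simulated trials of 80 × 28 days:

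| True effect | Estimate without interaction | Abstinence × day estimate | Interaction significant |
|---|---|---|---|
| −0.4 fading to 0 | −0.201 | 0.397 (true 0.4) | 80% |
| constant −0.2 | −0.201 | −0.005 (true 0) | 6% |

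The model without the interaction gives the same answer to both. The interaction separates them.

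**Step 3: shared trend with no true effect.** Let sleep(i,t) = c(i) + g × d + AR(1) error, and let the probability of abstinence change with d. Subtracting each person's mean leaves g × (d − mean d) in sleep and a slope in abstinence. The within-person covariance of the two is not zero, so bW is not zero. AR(1) weighting reduces the influence of slow changes but does not remove it.

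First set: abstinence independent from day to day given the person (person-level SD 1.2 on the logit scale), person intercepts removed, AR(1) correlation 0.3 in the data and estimated in the fit, 300 to 600 trials per scenario. Abstinence percentages are for the median person.

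| Sleep trend over 28 days | Abstinence | Rejection at nominal 5%, no day term | With linear day |
|---|---|---|---|
| none | flat 50% | 5% | 5% |
| 0.5 SD | flat 50% | 5% | 5% |
| none | 70% → 30% | 5% | 5% |
| 0.2 SD | 70% → 30% | 4–6% | 3–4% |
| 0.5 SD | 70% → 30% | 13–15% (bias about −0.04 SD) | 5% |
| 0.5 SD | 30% → 70% | 13% (bias about +0.04 SD) | 6% |
| 0.8 SD | 80% → 30% | 42% (−0.08 SD) | 4% |
| 1.0 SD | 80% → 30% | 59% (−0.10 SD) | 4% |

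Second set: abstinence falling from 75% to 29%, ICC 0.2, AR(1) correlation 0.3, 500 trials per scenario, varying the day-to-day persistence of abstinence.

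| Abstinence process | 0.5 SD sleep trend, no day term | 0.25 SD sleep trend, no day term |
|---|---|---|
| independent days | 25% (bias −0.05 SD) | 9% |
| persistent | 42% (−0.09 SD) | 14% |
| lapse leads to permanent relapse | 80% (−0.24 SD) | 30% |

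With linear day, rejection was 3–7% and bias about 0 in every scenario of this set. A further run with variance parameters treated as known (600 trials, 0.5 SD) gave 22% for independent days, 30% for persistent days, 26% with large differences between people, and 73% for permanent relapse.

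The 3–7% is compatible with 5%: for 300 trials the simulation standard error is √(0.05 × 0.95/300) = 0.013.

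**The case against.** The strongest reply is that this is a condensed article. The covariate list is introduced as examples, the cross-lagged figure is not available here, sensitivity analyses are promised without detail, and a time term is the sort of thing an analysis plan adds. This limits the wording: the accurate statement is that no stated term tests attenuation, not that the investigators have ruled one out or that attenuation can never be assessed. The data will exist and the term can be added. But the reply does not remove the point. The article does state the model and its covariates, and that model does not answer its own hypothesis. Even if day were a candidate for the stepwise procedure it might not be kept, and as a main effect alone it would not test attenuation.

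A reader might infer that the Hypothesis 1 estimate is biased towards the hypothesis. The documents do not support that. Bias needs a trend in both series, and the article gives neither. The Abstract's account of early lapses that tend to end in relapse, and the hypothesis's own appeal to withdrawal, make falling abstinence with recovering sleep plausible but do not establish it. If both rise, the sign reverses; if either is flat, the bias is negligible.

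A reader might also take a figure near the top of the simulated range as the error rate. At a 0.5 SD trend, rates above 70% arose only under permanent relapse; independent days gave 13% to 25%.

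The plan speaks of later changes in sleep, which may mean conditioning on the previous night. The simulations had no lagged outcome, so their figures could shift. Such a term would still not test attenuation.

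Finally, the Discussion remarks that "all participants will receive equal numbers of EMAs in this observational study, and those variables will be centered at the person mean". One could read this as claiming that centring removes reactivity to the assessments. The passage rests mainly on cited studies and says nothing about reactivity that changes with study day, so no fault is raised there.

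**Conclusion.** The point stands in two parts of different strength.

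The first depends on no assumed trend. Hypothesis 1 includes attenuation, and the stated models contain no term that could show it.

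The second is a conditional risk. Without day since quit, a shared post-quit trend can produce or distort an abstinence–sleep association, and neither centring nor AR(1) errors protects against it. For a 0.5 SD sleep trend with abstinence falling from about 70–75% to about 30%, the illustrative false-positive rate is about 13% to 80%, governed mainly by the persistence of abstinence, against about 3–7% with a linear day term. The trend sizes, the persistence and the residual correlation are assumptions. The simulations cover the model with sleep as outcome; the same reasoning applies with abstinence as outcome, but was not simulated.

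This point does not show the stated sample size to be wrong, although the power calculation does not address the interaction.

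**What to change.** - Include day since quit as a fixed effect in the models for both directions, outside the stepwise selection. Use a linear term, with a quadratic or weekly version as a check on non-linearity.
- Prespecify the within-person abstinence × day-since-quit interaction, in the models with sleep as outcome, as the test of the attenuation part of Hypothesis 1.
- Report the estimated abstinence effect with its confidence interval at set days, for example days 1, 7, 14 and 28.

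The cost is about two degrees of freedom, a sentence or two in the analysis plan, and no new data. It can be settled before recruitment opens in June 2026.

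For orientation, the article's first power step reproduces at 177 for six predictors. The same calculation gives 187 for seven and 196 for eight. The article's effective-sample formula gives 2,240/(1 + 27 × 0.2) = 350 for 80 people over 28 days at ICC 0.2, and 2,240/(1 + 27 × 0.4) = 189.8 at the upper end of its ICC range. The extra terms therefore fit easily at the planning ICC and are close to the limit at 0.4. That calculation is for the overall regression, so the precision expected for the interaction should be stated separately.
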